## Results

As of July 2022, a total of 45 individuals have been assessed as eligible for study enrollment (Multimedia Appendix 2).

Preliminary data showed adequate Cronbach α for all the T0 self-report questionnaire scores (ranging from .66 to .83). No differences emerged between the GI and VR groups at the baseline (T0) for all the sociodemographics and psychological features investigated (gender, marital status, school attendance, employment, participation in relaxation training in the past, use of VR in the past, anxiety, depressive and stress symptomatology, and the ability to imagine in a vividness way mental images) except for age (*F*_1,39_=12.32; *P*<.001) and years of education (*F*_1,39_=4.81; *P*=.04), factors that have been controlled for in the following group comparisons. To preliminarily investigate the differences between the VR and GI groups in experiencing state anxiety before and after the relaxation session (T1) and at T2, repeated-measures multivariate ANOVAs have been computed. At T1, our preliminary analysis showed a significant difference of the state-anxiety symptoms (*F*_1,39_=22.48*;*
*P*<.001) between groups with lower scores in state anxiety (VR group: mean 30.10, SD 4.35; GI group: mean 39.35, SD 4.71; *t*_1,39_=5.92*;*
*P*<.001) for the VR group after the relaxation session. Moreover, the VR group perceived a higher sense of physical presence (*F*_1,39_=7.38*;*
*P*<.01). The study’s experimental phase is expected to conclude in May 2023, and the results of the research will be presented in June 2023. The results obtained from this work will be published in an open-access scientific paper and in the form of posters and conference papers to be presented at national and international conferences.

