### Study Overview and Objectives

The purposes of the present research project are as follows:

Investigating if PMRT associated with a personalized relaxing scenario in VR can facilitate relaxation and lower state anxietyUnderstanding if the VR scenario helps recall the relaxing image assessed during the follow-up sessionInvestigating if VR is more effective in promoting the association between the relaxing scenario and PMRT than the standard procedure, consisting of PMRT associated with the imagery-induced exposure to a subjective relaxing environmentAnalyzing if the relaxing sessions administered via Zoom are more effective in managing anxiety and stress than a procedure administered via audio-tracks.

We hypothesize that VR would be more effective than GI in promoting relaxation and decreasing state anxiety because it would facilitate the visualization process, allowing individuals to have more realistic sensory experiences than imagery-induced exposure.

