### Study Design

The present protocol of the proof-of-concept study is a longitudinal, between-subjects, 3-armed randomized controlled trial aiming to compare three treatment conditions (Figure 1):

Active Comparator condition, consisting of the deployment of the PMRT training via Zoom and GI exposure. It consists of a standard behavioral intervention based on 4 individual PMRT sessions via Zoom (t1-t4), an in vivo PMRT relaxing session and GI conducted by a psychotherapist (T1) after a week from the baseline assessment (T0), and a follow-up phase (T2) after 2 weeks consisting in recovering the GI relaxing scenario and PMRT session (see Multimedia Appendix 1 and Figure 2).Intervention A is an experimental condition in which the complementary intervention is composed of the PMRT administered via Zoom integrated with a personalized VR exposure deployed by a head-mounted display (Oculus Quest 2). It comprises 4 individual PMRT sessions via Zoom (t1-t4), an in vivo PMRT relaxing session and VR exposure (T1) after a week from T0, and a follow-up phase that consists of the same activities as the Active Comparator condition (see Multimedia Appendix 1 and Figure 3).Intervention B is an experimental condition in which the complementary intervention is composed of progressive muscle relaxation training administered through an audio-track integrated with the same personalized VR exposure setup in Intervention A. It is composed of 4 individual PMRT sessions via an audio-track delivered on the Moodle platform (t1-t4), an in vivo PMRT relaxing session and VR exposure (T1) after a week from T0, and a follow-up phase that consists of the same activities as the Active Comparator and the Intervention A conditions (see Multimedia Appendix 1 and Figure 4).

The assessment phases take place at baseline (T0), before and after the 4 PMRT sessions (via Zoom or audio-track), at the fifth in-presence session (T1), and a week later (T2).

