The T1 phase (day 7) required approximately 60 minutes. Before and after the relaxation session, states of tension and anxiety are assessed by using a 0 (no tension) to 10 (extreme tension level) scale, and the state-anxiety level is evaluated based on the STAI-Y1. Then, participants are exposed to a PMRT session merged with a VR or a GI procedure. Before the GI or the VR experience, all the participants fill out the Vividness of Visual Imagery Questionnaire and the Test of Visual Imagery Control. After the PMRT session, users compile a series of self-report questionnaires investigating depression, anxiety, stress, and quality of life (STAI-Y, DASS-21, PGWBI), and the VR group only fill out the Virtual Reality Sickness Questionnaire to monitor VR-related side effects (eg, sickness) and the ITC-SOPI to assess the sense of presence at the end of the T1 phase. The Mi Band 2 sensor is used during the entire T1 phase administration to detect resting heart rate activity. This assessment phase is administered through the Moodle e-learning platform.

The T2 phase (follow-up) is deployed for approximately 45 minutes. Before and after the relaxation session, states of tension and anxiety are assessed using a visual analog scale from 0 (no tension) to 10 (extreme tension level). The state-anxiety level is evaluated based on the STAI-Y1. All the users are exposed to a self-GI experience in which those who were part of the VR group are asked to recall the personalized VR scenario experienced during the T1 phase (day 7). Instead, the GI group retrieve the image participants had used in association with the PMRT during the T1 phase (day 7). After the session, participants fill out a series of self-report questionnaires investigating depression, anxiety, stress, quality of life (STAI-Y, DASS-21, PGWBI), and an ad hoc version based on the ITC-SOPI to assess the sense of presence experienced during the imagery experience. This assessment phase is administered based on the Moodle e-learning platform. The Mi Band 2 sensor is used during the entire T1 phase administration (day 7) to detect resting heart rate activity.

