### Measures-Screening and Primary Outcomes

In Table 1, all the assessment and primary outcome measures are described.

**Table 1 table1:** Evaluation tools and methods by outcome of interest.

Primary objective	Description	Evaluation tool
1. Number of participants with virtual reality (VR)–related side effects as assessed by the Virtual Reality Sickness Questionnaire (VRSQ) and the investigators’ observations^a^	Participants in the 2 VR experimental arms (Interventions A and B) are asked to refer to whether the VR head-mounted display was painful, too heavy, or uncomfortable. Participants are asked if they have experienced negative side effects during the VR exposure based on the VRSQ, administered at the end of the VR exposure. This questionnaire is based on a dichotomous answer (Yes/No). During the VR experience, the investigator observes participant reactions and records the behaviors and signs that suggest an unpleasant experience.	VRSQ [44,45]
2. Changes between and within subjects in depression scores^b^	Differences between groups and change from baseline to the T1 and T2 phases in depression scores are assessed based on the Depressive Anxiety Stress Scale-21 (DASS-21-Depression Subscale). Items are answered using a 4-point Likert scale (0-3). Scores range from 0 to 42 (the scores will need to be multiplied by 2 to calculate the final score). Higher scores indicate more severe depression.	DASS-21-Depression Subscale [46-48]
3. Change is being assessed between and within subjects in trait-anxiety scores^b^	Differences between groups and change from baseline to the T1 and T2 phases in trait-anxiety scores are assessed based on the State-Trait Anxiety Inventory-Y2 (STAI-Y2, Trait Anxiety). The measure is a self-report questionnaire investigating trait anxiety based on a 4-point Likert scale (1-4). Scores range from 20 to 80. Higher scores indicate higher trait-anxiety severity.	STAI-Y2 [49-51]
4. Changes between and within subjects in state-anxiety scores^b^	Differences between groups and change from baseline to the T1 and T2 phases in state-anxiety scores are assessed based on the State-Trait Anxiety Inventory-Y1 (STAI-Y1, State Anxiety) before and after each session. The STAI-Y1 is a self-report questionnaire investigating the state anxiety based on a 4-point Likert scale (1-4). Scores range from 20 to 80. Higher scores indicate greater state-anxiety severity.	STAI-Y1 [49-51]

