### Statistical Procedure and Data Analysis

Quantitative statistical analyses will be performed using SPSS (versions 27.0 and 28.0; IBM Corp) [60,61] and R package [62]. To investigate the normal data distributions of the dependent variables, ranges of skewness and kurtosis will be determined. The Kolmogorov-Smirnov and the Shapiro-Wilk tests will also be performed to evaluate the statistical significance (mean, 95% CI) and normality of the distributions. In addition, Cronbach α will be assessed for each self-report questionnaire’s subscales. To explore sociodemographic features, frequencies, means, and SDs will be measured.

To examine differences between and within subjects, the 3 groups will be evaluated by a repeated-measures ANOVA for mixed designs, where individuals will be the random effect, while the type of intervention and time (T0/T1/T2/before and after each session) will be the fixed effects. The Akaike information criterion and binary logistic regression will be performed to explore significant influence factors.

Spearman rank correlation coefficient will be used to investigate the relationship between the self-reported measures and heart rate.

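### The reported VR v GI comparison does not say which VR arms it contains; if it pools Interventions A and B, as it appears to, the VR effect is mixed with Zoom v audio training

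*Protocol article*

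**What the plan says.** Study Design defines the arms by two features, how the relaxation training is delivered and what follows it:

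- Comparator: "Active Comparator condition, consisting of the deployment of the PMRT training via Zoom and GI exposure".
- Intervention A: "the complementary intervention is composed of the PMRT administered via Zoom integrated with a personalized VR exposure".
- Intervention B: "progressive muscle relaxation training administered through an audio-track integrated with the same personalized VR exposure setup in Intervention A".

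No arm combines audio training with guided imagery.

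Study Overview and Objectives states the main hypothesis: "We hypothesize that VR would be more effective than GI in promoting relaxation and decreasing state anxiety". Zoom v audio delivery is a separate purpose in the same section.

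Statistical Procedure and Data Analysis says that "the 3 groups will be evaluated by a repeated-measures ANOVA for mixed designs", with type of intervention as a fixed effect. It ties no particular contrast to the VR hypothesis.

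Results reports a preliminary comparison: "To preliminarily investigate the differences between the VR and GI groups in experiencing state anxiety before and after the relaxation session". It has one VR group, one GI group and 1 numerator degree of freedom. It is adjusted for age and years of education. Training mode is not among the stated adjustments, A and B are not named, and no numbers per arm are given. The Discussion relies on this comparison when it says, for the main objective, that VR lowered state anxiety more than GI did.

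**The concern.** A and the Active Comparator share Zoom training, so their difference is the VR effect. B differs from the Active Comparator in two ways at once, and one of them (audio v Zoom) is a factor that the trial sets out to study in its own right. A VR group made of A and B together therefore does not estimate the VR effect unless delivery mode makes no difference.

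The article's own usage points to such a group. Study Design says that at T1 "the VR group only fill out the Virtual Reality Sickness Questionnaire", while Table 1 assigns that questionnaire to "Participants in the 2 VR experimental arms (Interventions A and B"). The T2 description likewise divides all participants into a VR group and a GI group.

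At stake is the article's main conclusion. If Zoom training works better than audio, pooling hides part of the VR benefit. If audio works better, pooling adds to it.

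**Working it through.** **1. The plan's own figure.** Power Calculation gives f = 0.25, α = 0.05, power 0.80, 3 groups and 3 measurements. For the between-factor test, λ = f²·N·m / (1 + (m − 1)ρ). With ρ = 0.5 (assumed; not stated) and N = 108, λ = 0.0625 × 108 × 3 / 2 = 10.125, and power is 0.809. The stated 36 per group reproduces. It is the sample size for a three-group overall test, not for a VR contrast and not for a pooled one.

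**2. What pooling would estimate.** Let C, A and B be the arm means and s the share of B in the VR group.

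Pooled VR − GI = (1 − s)A + sB − C = (A − C) + s(B − A).

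The first term is the VR effect and the second is s times the audio-minus-Zoom difference.

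| Make-up of VR group (A/B) | s |
|---|---|
| 36/36 | 0.50 |
| 14/13 | 0.48 |
| 15/5 | 0.25 |
| A only | 0 |

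The documents give no delivery effect. For an assumed audio-minus-Zoom difference of −5 to +5 STAI points and s = 0.5, the shift is −2.5 to +2.5 points. Lower STAI is better, so if Zoom is better the difference is positive and the VR benefit is understated.

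**3. Can the printed figures show who was in the VR group?** Inputs from Results: VR 30.10 (SD 4.35), GI 39.35 (SD 4.71), difference 9.25, t = 5.92, F = 22.48. The Abstract gives 40 participants; Results gives 45 eligible as of July 2022.

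- *Allocation.* If the 40 are a subset of the 45 and B was left out, B held at most 5 of 45. Under equal simple allocation, P(X ≤ 5) for Binomial(45, 1/3) is 0.0006. This favours pooling, but the 40 are undated.
- *t value.* The pooled-variance t from the means and SDs is 6.45 at 20 VR/20 GI, 6.13 at 27/13, 5.87 at 29/11 and 5.96 at 13/27. The printed 5.92 fits a split near 2:1 in either direction.
- *Means.* If these are raw means of integer totals, 30.10 and 39.35 are both possible, for 40 people, only at 20/20 (602/20 and 787/20). At 27/13 neither is possible: 813/27 = 30.11 and 812/27 = 30.07; 512/13 = 39.38 and 511/13 = 39.31. If A and B were pooled under 1:1:1 allocation, P(GI ≥ 20 of 40) = 0.021.
- *Reliability.* 5.92² = 35.0, not 22.48, and covariates were used, so neither the t value nor the means need be raw quantities.

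These clues conflict. The composition of the VR group cannot be recovered from the text.

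**4. Illustration only: a pooled test at the planned size.** Two-sided 5% test, single occasion, no covariate, equal A and B, assumed delivery effects in SD units:

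| Delivery effect | Bias (half) | False-positive rate, no VR effect | Power, true VR effect 0.5 SD, bias against VR |
|---|---|---|---|
| 0.2 | 0.10 | 8% | 49% |
| 0.3 | 0.15 | 11% | 40% |
| 0.5 | 0.25 | 23% | 23% |

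A v Active Comparator (36 v 36) has 55% power at 0.5 SD, with no such bias.

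**5. Price of the clean contrast.** In SD units the standard error is √(1/36 + 1/36) = 0.236, against √(1/72 + 1/36) = 0.204 for the pooled contrast. The ratio is 1.155.

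**The case against.** The strongest reply is that the planned analysis does not pool. It keeps three groups, the sample size is for three groups, and A v Active Comparator can be read from the planned model without changing its fit. The two-group comparison is a preliminary look, and the Discussion says that the matter will be examined fully once recruitment ends. A condensed article may also leave pairwise contrasts to an analysis plan. Most of this stands, and it limits the point. It does not remove it: the article reports a two-group VR v GI test and draws a conclusion for its main objective from it, and a three-group overall test does not by itself answer a VR v GI hypothesis.

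A reader might infer three stronger things that the documents do not support:

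- *That the VR group must contain B.* The article's usage and the allocation argument favour this. However, no arm counts are printed, the 40 are undated, the means fit equal groups, and the t value fits 13/27 as well as its reverse.
- *That the final analysis will suffer the error rates in step 4.* No 72 v 36 test is stated anywhere.
- *That pooling explains the reported 9.25-point advantage.* With equal A and B, delivery alone would need audio to beat Zoom by 18.5 points, about 4 SD (18.5/4.53). If Zoom is better, pooling works against VR.

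**Conclusion.** The point holds with moderate confidence. It is certain from the design that only A v Active Comparator isolates VR, and that the reported VR v GI comparison does not identify its arms. It is likely, but not established, that this comparison pools A and B. If it does, the VR estimate contains s times the audio–Zoom difference, with s = 0.5 for equal A and B; the size and sign of that difference are unknown. If the VR group is A alone, there is no such bias and only the reporting is deficient. The planned three-group analysis is not itself biased; its gap is that its overall test does not address the stated hypothesis.

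**What to change.** In Statistical Procedure and Data Analysis, within the planned three-group model, name two contrasts: A v Active Comparator as the test of the VR v GI hypothesis, and B v A as the test of delivery mode. Equivalent coding is a VR indicator (1 for A and B, 0 for the Active Comparator) plus an audio indicator (1 for B only). Report any pooled A+B v GI result as secondary and labelled as mixed with delivery mode.

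In Results, state which arms form the VR group and give the number per arm. If A and B were pooled, redo the comparison as A v Active Comparator, and bring the Discussion into line with the result.

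The cost is a sentence or two and a re-run of the preliminary comparison. The clean contrast uses 36 v 36 rather than 72 v 36, so its standard error is about 15% larger.

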## Discussion

This study aims to evaluate the impact of exposure to customized natural and realistic VR-based scenarios as a factor that may enhance relaxation when administered with PMRT. To our knowledge, few studies have addressed this topic [63].

Furthermore, in light of the COVID-19 pandemic, innovative VR treatment protocols are increasingly requested and helpful in managing relaxation, also due to the possibility to be administered with larger flexibility in several different contexts and partially independent from the presence of the therapist [64].

Moreover, delivering an entire PMRT protocol with a psychotherapist present may require a considerable amount of time and higher costs. The introduction of VR may positively reduce intervention costs, as it allows partial self-management of the treatment. Furthermore, in the case of patients with medical problems (eg, cancer), the integration of VR may facilitate the administration of the relaxation intervention during specific invasive treatments (eg, chemotherapy sessions).

Assessing the efficacy of PMRT in alternative ways could extend the treatment administration, especially in situations where the standard delivery procedure is more difficult to implement.

With the aim to preliminarily investigate this study’s main objective, initial analyses showed that VR with PMRT facilitates a greater decrease of state anxiety than GI. Based on our knowledge, no studies have investigated VR with PMRT as an alternative complementary technique instead of GI. The current findings are promising and will be extensively investigated at the end of the recruitment phase.

This study is characterized by a series of limitations that should be considered and solved in the implementation of future studies. First of all, it is essential to consider the prominent role that psychophysiological parameters have in measuring relaxation, defined as the ability of the human body to reduce physiological arousal, and which can be assessed by measuring a decrease in muscular tension, heart rate, respiration rate, and sweating rate [3,65]. Although our project is targeted at investigating a self-reported sense of presence, engagement, and relaxation feeling, it should be important to also investigate psychophysiological measures other than heart rate, such as breathing rate, heart rate variability, galvanic skin response, cortical levels, and changes in brain wave activities. Research conducted so far investigated these parameters to understand the impact of distinct VR-based relaxation techniques different from progressive muscle relaxation, showing promising results [3]. Moreover, it would be important to thoroughly investigate psychophysiological activity also when VR is merged with PMRT both with clinical and nonclinical samples.

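### The Discussion says VR was shown to reduce state anxiety more than GI, but the Results report only post-session levels at T1, so a greater decrease is not shown in the article

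*Protocol article*

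**What the plan says.** **Discussion.** On the study's main objective, the article says that "initial analyses showed that VR with PMRT facilitates a greater decrease of state anxiety than GI", and goes on to call the findings promising.

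**Results.** The analysis is described as covering state anxiety "before and after the relaxation session (T1) and at T2, repeated-measures multivariate ANOVAs have been computed". The reported finding begins "At T1, our preliminary analysis showed a significant difference of the state-anxiety symptoms" and gives F=22.48, described as a difference between groups. The scores are "VR group: mean 30.10, SD 4.35; GI group: mean 39.35, SD 4.71", with t=5.92, and are placed in time by the words "for the VR group after the relaxation session". No other state-anxiety score is given.

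On comparability, the same section says "No differences emerged between the GI and VR groups at the baseline (T0) for all the sociodemographics and psychological features investigated". Anxiety is in the list of features. The stated exceptions are age and years of education, which the article says were controlled for in the later comparisons.

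**Study Design.** STAI-Y1 is taken before and after the session at both T1 and T2. VR exposure first occurs at T1, after four training sessions. Training is by Zoom in the Active Comparator and Intervention A, and by audio-track in Intervention B.

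**Table 1.** The state-anxiety outcome is defined through differences between groups and change from baseline to T1 and T2, measured before and after each session.

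**The concern.** A lower level after the session is not the same quantity as a larger fall. If the groups already differed when they arrived for T1, VR cannot have caused that part of the gap, because exposure had not begun. About a week and four training sessions separate T0 from T1. If the VR group pools Interventions A and B, part of it was also trained by a different mode from the GI group.

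The article's answer to its main question rests on this sentence. The Statistical Procedure section puts T0, T1, T2 and before/after each session into one time factor, without saying which contrast compares VR with GI at T1. If post-session levels were again described as a decrease, a gap that existed before exposure could be credited to VR.

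**Working it through.** **1. Inputs.** From the Results: VR mean 30.10, SD 4.35; GI mean 39.35, SD 4.71; t=5.92; F=22.48. From the Abstract: 40 participants in the preliminary data. The VR/GI split is not given. The printed degrees of freedom (39) would imply 41 people in a pooled t test, so both totals were tried.

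**2. What the t statistic tests.** The difference is 39.35 − 30.10 = 9.25. The pooled statistic is t = 9.25 / [s_p × √(1/n₁ + 1/n₂)]; the Welch statistic is t = 9.25 / √(4.35²/n₁ + 4.71²/n₂).

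| VR / GI (assumed) | pooled t | Welch t |
|---|---|---|
| 20 / 20 | 6.45 | 6.45 |
| 27 / 13 | 6.13 | 5.96 |
| 29 / 11 | 5.87 | 5.66 |
| 30 / 11 (N=41) | 5.90 | 5.69 |

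The printed 5.92 is matched closely, though not exactly, by an unequal split. The reverse direction fits as well (13 VR / 27 GI: 5.96 pooled), so the t does not settle which group was larger. It is consistent with a two-sample test of post-session levels and uses no pre-session score.

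**3. What the F statistic tests.** 5.92² = 35.05, not 22.48. The F is therefore not the square of that t. It is a different or covariate-adjusted test, and the text does not name its effect.

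**4. The quantity the Discussion claims.** For each group, decrease = pre − post. The extra decrease with VR is therefore (post GI − post VR) − (pre GI − pre VR) = 9.25 − pre-session gap. The gap is not reported, so the result cannot be computed. With assumed values:

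| Pre-session gap, GI minus VR | Extra decrease with VR |
|---|---|
| 0 | 9.25 |
| 3 | 6.25 |
| 6 | 3.25 |
| 9.25 | 0 |
| 12 | −2.75 |

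**5. How far the T0 statement helps.** Assume that the T0 comparison used STAI-Y1 at the two-sided 5% level with 20 per group. The largest non-significant gap is t(0.975, 38) × SD × √(2/20). This is 2.9 points for SD 4.5, 4.5 for SD 7, 6.4 for SD 10 and 7.7 for SD 12. These SDs are assumptions; the article gives no T0 state-anxiety mean or SD. Of the 9.25 points, between 6.4 and 1.6 would remain as extra fall from T0.

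**6. The choice of contrast for the final analysis.** Take a standardised effect of 0.5 (assumed), 36 v 36 from the Power Calculation section, two-sided 5%, equal pre and post variances, and pre-post correlation r (assumed). The standard error relative to a post-only comparison is √(1 − r²) with adjustment for the pre-session score, and √[2(1 − r)] for change scores.

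| Contrast | SE ratio, r=0.5 | Power | SE ratio, r=0.7 | Power |
|---|---|---|---|---|
| Post-session only | 1.00 | 55% | 1.00 | 55% |
| Change score (arm by pre/post) | 1.00 | 55% | 0.77 | 77% |
| Post, adjusted for pre | 0.87 | 68% | 0.71 | 83% |

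The adjusted difference and the arm by pre/post test are different estimators with different precision, so one has to be chosen.

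**The case against.** Several points on the other side stand.

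- **Comparability at T0.** Allocation was random, no anxiety difference was found at T0, and age and education were controlled for. Table 1 defines change from baseline as well as within sessions, and the Discussion does not say that the decrease is within the T1 session. A lower T1 level is then reasonable, if loose, evidence of a larger fall from T0. What limits it: non-significance is not equality, the T0 anxiety scale is not named, and T0 is not entry to T1.
- **The F test.** It is attributed to a repeated-measures analysis that includes the pre-session score, and it could be the interaction. If so, naming it would support the sentence.
- **Chance imbalance.** Under randomisation, the standard error of the post-session comparison already reflects chance differences at entry. They are not an extra error to set against the reported P value.
- **Planned model and hedging.** The planned mixed model already includes pre-session scores, and the results are labelled preliminary.

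A reader might go further and infer that VR gives no greater decrease, or that T2 was left out because it was unfavourable. The documents support neither. A post-session difference of 9.25 points is large, and the T2 result is simply unknown: its absence is a reporting gap, with no motive implied.

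**Conclusion.** The point holds as one about what the article demonstrates. The Discussion says a greater decrease was shown. The Results support a lower post-session state-anxiety level with VR at T1, by 9.25 points, and nothing further that a reader can verify. A larger fall from T0 is plausible. The fall within the T1 session could be anything from the full 9.25 points to none, depending on an unreported entry gap.

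The missing evidence is the T1 pre-session means, a named group-by-time effect and the T2 state-anxiety result. The conclusion rests on the printed text alone and would change if F=22.48 were identified as the group-by-pre/post interaction. The assumed splits, SDs and correlations serve only to show the range.

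This is a modest correction. It deserves making because it concerns the main objective and because the contrast for VR v GI at T1 is still open.

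**What to change.** 1. **Discussion.** Say that VR was followed by lower post-session state anxiety at T1. If F=22.48 is the group-by-pre/post interaction, name it as such in the Results; the present sentence can then stand.
2. **Results.** Report T1 pre- and post-session STAI-Y1 means (SD) per arm, the between-arm effect with its 95% CI, and the T2 state-anxiety result whatever it shows.
3. **Final analysis.** Name one contrast in advance for VR v GI at T1. Preferably this is post-session STAI-Y1 adjusted for T1 pre-session STAI-Y1, for Intervention A v Active Comparator, where training before T1 is the same.
4. **Intervention B.** Its T1 pre-session score follows audio-track training, so adjusting for that score removes any effect of training mode. Adjust for T0 STAI-Y1 there, or state that the estimate concerns the T1 session only.

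The cost is a re-run on data that the design already collects, one reworded sentence and one added line in the analysis section. The downside is that the preliminary statement may become less favourable.
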